Apart from potential structural differences, functional neuroplasticity will also be assessed. A lesser degree of cognitive involvement during movement execution may be associated with lower activation in the sensorimotor cortex (Cheng et al., 2015). On the other hand, increased cognitive involvement may be expected in variable conditions due to, e.g., due to stimulus identification or decision making. Therefore, an assumption that decreased cognitive involvement and, as a result, decreased prefrontal cortex activation in constant practice conditions sounds reasonable. Moreover, we may hypothesize that practicing and learning in constant conditions will be characterized by lower sensorimotor cortex activation since there will be decreased control during the motor performance, which leads to more adaptive motor performance. Vernon and colleagues (Vernon et al., 2003) showed that in order to reduce the somatosensory interference in information processing, their participants enhanced SMR power as indexed by increased SMR/theta and SMR/beta ratios. As a result, participants were able to maintain perception and, to a lesser extent, focused attention. Assuming that parametrization has to take place under variable practice conditions every time one changes performance from one variation of skill to another, demand on cognitive resources (perception and attention) would be bigger than in constant conditions, in which parametrization is facilitated. Consequently, the variable practice group should increase SMR as compared to the constant practice conditions group.

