There have been no previous studies on cortical networking in constant and variable practice and motor learning; we decided to assess such communication measuring EEG coherence (Deeny et al., 2009). A significant linear relationship exists between time series simultaneously recorded from two locations (high coherence), indicating communication between these areas of the cerebral cortex. In contrast, low coherence indicates the opposite (Deeny et al., 2009). We may expect decreased coherence between premotor (Fz) and motor (C3, C4) areas of the cortex and between the premotor and occipital regions as the practice of a visuo-motor task progresses (Busk and Galbraith, 1975). However, if the constant and variable practice condition groups receive the same amount of practice, we may expect that pairing electrodes in specific regions will be undifferentiated (Deeny et al., 2003). Lelis-Torres and colleagues (Lelis-Torres et al., 2017) noted that when investigating the cognitive effort involved in random compared to constant practice schedules, the random practice induced significantly greater cognitive effort than constant practice. Throughout the practice, both task engagement and mental workload decreased more in the constant practice condition than in the random practice condition. However, the random schedule is only one variant of variable practice. Another extreme is the blocked practice schedule. Variable practice in blocked order assumes that a learner is practicing many skill variations but in blocks (or time). Although, authors agree that this is also variable practice (Van Rossum, 1987; Czyż, 2021), some doubt whether this variability differs from constant practice (Kim et al., 2021b). This ambiguity will be tested in our study.

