The participants from VG will perform three types of SPSICs (1–3), each repeated 15 times (together 45 trials), but the participants from CG will perform 45 times of one type of SPSIC. This SPSICs will be analyzed in the frequency domain using force signal as a trigger for extracting SPSIC sequences related to time frames of EEG time series data. We will estimate EEG signal’s power spectrum density (PSD) for sensorimotor rhythm (SMR, frequency band 12–15 Hz) as well as for other frequency bands: delta (0.5–4 Hz), theta (4–8 Hz), alpha (8–14 Hz), beta (14–35 Hz) and gamma (35–70 Hz). PSD-EEG analysis will reveal the level of the electrical activity of cortical regions engaged during UIFA motor tasks performance under the constant and variable practice conditions. We will also estimate coherence between EEG signals (EEG-EEG coherence) from electrodes in a chosen region of interest based on the PSD-EEG analysis. Analysis of EEG-EEG coherence calculates the linear relationship between the power spectra of two EEG signals taken from two EEG electrodes placed on the scalp. A significant linear relationship existing between time series simultaneously recorded from two locations (high coherence) indicates a high level of functional communication (connectivity) between these areas of the cerebral cortex, whereas low coherence indicates the opposite.

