### Statistical Methods

#### Statistical Methods for Primary and Secondary Outcomes

In order to compare groups practicing in constant and variable practice conditions in terms of brain’s structural and functional changes, repeated measures ANOVA with time as a within-participants factor, and practice condition as a between participants factor, with *post-hoc* tests will be used. The relationship between MRI brain changes and motor task proficiency will be evaluated using partial correlations.

Frequency analysis will be performed separately for each EEG channel and trial using fast Fourier transform (FFT). Significant differences against baseline will then be compared between participant groups. Connectivity analysis will be performed using the calculation of coherence (Nunez et al., 1997, 1999) between channels of interest. Results will be statistically compared between participant groups. Because of the multiple usages of statistical tests, multiple comparison corrections will be used.

Motor task proficiency will be assessed using parametrical or non-parametrical tests, depending on the results of the assumption tests (homogeneity, normality). The possible tests include but are not limited to correlations, t-test, and analysis of variance (2 × 3 model; two practice conditions × three time points) with the following *post-hoc* analysis for all significant main effects.

We may use Bayesian equivalents of the tests mentioned above.

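### Significant coherence between two scalp electrodes is read as cortical communication, although a source seen by both electrodes produces it without coupling, and a power change that differs by arm can then mimic an arm difference in connectivity

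*Protocol article*

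**What the plan says.** Primary outcome 2 (Outcomes) includes coherence during the step-contraction (SPSIC) task. It is calculated from "two EEG signals taken from two EEG electrodes placed on the scalp", with the electrodes taken "from electrodes in a chosen region of interest based on the PSD-EEG analysis". The article then gives the interpretation: "A significant linear relationship existing between time series simultaneously recorded from two locations (high coherence) indicates a high level of functional communication (connectivity"). Background and Rationale reads high coherence the same way, as "indicating communication between these areas of the cerebral cortex", and adds: "In contrast, low coherence indicates the opposite".

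Under Statistical Methods for Primary and Secondary Outcomes, "Connectivity analysis will be performed using the calculation of coherence" between channels of interest, and "Results will be statistically compared between participant groups". Connectivity between cortical areas is named in primary objective 2.

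On power, Background and Rationale predicts that "the variable practice group should increase SMR as compared to the constant practice conditions group". Source analysis with co-registration to individual T1 scans is described under Outcomes, but for the motor-related cortical potential (MRCP) recordings and not for SPSIC coherence.

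**The concern.** Each scalp electrode records a mixture of sources. A source that reaches two electrodes does so at zero lag and makes the two signals linearly related even if the cortical areas beneath them are independent. A significant linear relation between scalp signals therefore does not establish communication between areas.

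The size of this spurious coherence depends on how strong the shared source is relative to everything else at the two electrodes. If practice changes that power differently in the two groups, coherence can differ by arm with connectivity unchanged, and a power effect would be reported a second time as a connectivity effect. Two features of the plan make this more than theoretical: SMR power is expected to differ by arm, and the coherence electrodes are picked from the power results.

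**Working it through.** The protocol states no figure on this point, so there is none to reproduce. The check is algebra plus simulation.

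**Inputs from the protocol.** 25 participants per group (Sample Size); 45 SPSIC trials per participant at each test in both groups (Outcomes); coherence at electrode level, compared between groups.

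**Assumptions not in the protocol.** One spectral segment per trial (L = 45); two-sided 5% level; complex-Gaussian sources; the leakage, shared-to-local ratios and power changes shown below.

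**Step 1: coherence without coupling.** Two independent sources with powers p1 and p2 leak into the other electrode with amplitude a, with sensor noise v. The magnitude-squared coherence is

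MSC = [a(p1 + p2)]² / [(p1 + a²p2 + v)(a²p1 + p2 + v)].

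With p1 = p2 = 1, v = 0.5 and a = 0.3: (0.6)² / (1.59 × 1.59) = 0.36 / 2.528 = 0.142. The values at a = 0.1, 0.2 and 0.5 are 0.018, 0.067 and 0.327. For scale, the 5% critical value for zero coherence with 45 segments is 1 − 0.05^(1/44) = 0.066. Leakage alone can therefore pass for significant coherence.

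**Step 2: arm comparison, leakage only.** With equal source power in both arms and 25 per arm, a t-test on transformed coherence rejected in 4.8% to 5.4% of simulated trials (a = 0.2 to 0.5, v = 0.5 to 1). Leakage that is the same in expectation in both arms does not produce an arm difference.

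**Step 3: arm comparison, with a power change in one arm.** Give both electrodes one common source whose power is r times the local power, with no coupling. Then MSC = [r/(1 + r)]². For r = 0.25 this is 0.2² = 0.040. If the common source doubles, r = 0.5 and MSC = (0.5/1.5)² = 0.111, although nothing about connectivity has changed.

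The simulated test is a t-test on the pre-to-post change in Fisher-z coherence, 25 per arm, with log-power SD 0.5 between and 0.2 within persons. The common source changes in one arm only. False-positive rates:

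| Shared-to-local ratio | no change | 1.25-fold | 1.5-fold | 2-fold |
|---|---|---|---|---|
| 0.1 | about 5% | 7% | 12% | 35% |
| 0.25 | about 5% | 14% | 34% | 82% |
| 0.5 | about 5% | 18% | 55% | 96% |

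Repeat runs moved these by up to about 3 points (84% in place of 82%, for example). The two-source leakage model of Step 1, with all source power higher in one arm, gives the same direction: 8% to 22%, 14% to 57% and 32% to 95% at power ratios of 1.25, 1.5 and 2.

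**Step 4: would a zero-lag-insensitive measure cure it?** With no coupling in either arm, the imaginary part of coherency rejected at about 5% throughout. Now add the same true lagged coupling (90 degrees) to both arms, with a 2-fold change in the shared source in one arm at ratio 0.25:

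| True coupling, equal in both arms | Ordinary coherence | Imaginary coherency |
|---|---|---|
| 0.3 | 47–53% | 16–18% |
| 0.5 | 15–18% | 40–41% |
| 0.7 | 6–7% | 75–78% |

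The weighted phase-lag index gave 26% and 52% at coupling 0.5 and 0.7. These measures remove spurious coherence from mixing, but they still move with power once real lagged coupling exists.

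**The case against.** Several points on the other side are sound.

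- **The planned test is between groups.** A reader might infer from Step 1 that the connectivity outcome is bound to be positive. Within-participant tests of zero coherence would indeed reject often (12%, 37%, 94% and 100% at leakage 0.05, 0.1, 0.2 and 0.3 without sensor noise), but Statistical Methods plans no such test as an endpoint. Those rates show that the stated interpretation fails. They are not error rates of the planned analysis.
- **Volume conduction alone does not bias the arm comparison.** Step 2 confirms this. A power change that differs by arm is also needed.
- **The Background gives a direction for SMR only.** It states no magnitude, does not place the change in a source shared by the electrode pair, and makes no such prediction for power in the other bands. It also expects electrode pairings not to differ between groups given equal practice, and the pairs it names are regional ones whose leakage is unknown.
- **SPSIC coherence is not the only connectivity evidence.** The MRCP recordings have their own source and connectivity analyses. These do not repair the SPSIC coherence, which stays at electrode level.
- **Reference, spatial filter and preprocessing may be in a fuller document.** Their absence from an article is not the point here. The point is an inference that the article states in two places and that would remain wrong whatever the preprocessing section says about other steps.
- **Replacing coherence outright is not clearly better.** Step 4 supports this: with substantial true lagged coupling the replacement can do worse.

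**Conclusion.** The statement that significant scalp coherence indicates communication between cortical areas is wrong as written and should be changed. The group comparison of coherence is not invalid in itself: it holds its 5% level under leakage alone. It becomes misleading if the power of a source seen by both electrodes changes differently by arm, which the protocol makes plausible for SMR. The false-positive rate is then about 7% to 35% at a shared-to-local ratio of 0.1 and about 14% to 84% at 0.25, for 1.25- to 2-fold changes in one arm.

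The direction of the effect is firm. The sizes rest on assumed ratios, power changes, variance components and one segment per trial, none of which the protocol supplies. The documents do not support the stronger readings that the arms will differ through volume conduction alone, or that ordinary coherence must be abandoned.

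**What to change.** 1. In Background and Rationale and in Outcomes, delete the statement that significant scalp coherence indicates communication (and low coherence the opposite), or limit it to say that scalp coherence also reflects sources common to both electrodes.
2. In Outcomes and Statistical Methods, keep the planned coherence. For the same channel pairs and bands, add one zero-lag-insensitive measure, named in advance: imaginary coherency or the weighted phase-lag index.
3. Report the arm difference in band power at those same channels beside it.
4. State the reading rule: an arm difference in coherence is interpreted as a connectivity difference only if the zero-lag-insensitive measure supports it and the band-power difference does not explain it. Both conditions are needed, because the added measure also moves with power when true lagged coupling exists.

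The cost is some wording and a little more analysis on the same recordings, with no new data. The downside is that true zero-lag coupling would not be claimed as connectivity. Keeping ordinary coherence preserves comparability with earlier coherence studies.

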### Participant Timeline

The schedule of enrolment, interventions, and assessments is presented in Table 1 (according to SPIRIT Statement).

**Table 1 T1:** Schedule of enrolment, interventions, and assessments.

	**Study period**					
	**Enrolment**	**Allocation**	**Post-allocation**			**Close-out**
**Timepoint**	** *Week 0* **	Week 0	** *Week 1* **	** *Week 2* **	** *Week 3* **	** *5-days retention test (Week 4)* **
**Enrolment**				
Eligibility screen	X				
Informed consent	X				
Allocation		X			
**Interventions**				
*Constant practice*			X	X	X
*Variable practice*			X	X	X
**Assessments**				
*Demographic information*	X	X			
*EEG*		X			X	X
*MRI*		X			X	X
*Motor task proficiency*		X	X	X	X	X

### Sample Size

In order to calculate the sample size, we used mean and standard deviation (SD) values (Dean et al., 2013) presented by Cheng and colleagues in Table 1, specifically, values for Time Window 1 (T1) for novice and expert participants (Cheng et al., 2015). We set confidence interval = 95%; power = 0.8; ratio of sample size = 1 (constant practice group vs. variable practice group). As a result, a minimal sample size estimated was eight participants in total, four participants per group. Given, we were going to recruit novices for both groups, the possible drop-out, statistical requirements (e.g., at least five observations perc variable in regression models), and considering potential recording problems, we decided to measure 25 participants per group.

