### Assignment of Interventions: Allocation

#### Sequence Generation, Concealment Mechanism, and Implementation

All participants will be randomly assigned to the constant and variable practice condition groups (CG and VG, respectively) with a 1:1 allocation ratio. An online randomization generator^1^ with three blocks of four, three blocks of six, and two blocks of 10 participants will be used.

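### The stated power of 0.8 rests on an expert-versus-novice contrast and is not re-derived for the novice-versus-novice comparison that the trial makes with 25 per group

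*Protocol article*

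**What the plan says.** The Sample Size section takes its means and SDs from one table of a cited study: "specifically, values for Time Window 1 (T1) for novice and expert participants". The settings follow: "We set confidence interval = 95%; power = 0.8; ratio of sample size = 1 (constant practice group vs. variable practice group"). The result is "As a result, a minimal sample size estimated was eight participants in total, four participants per group". The next sentence opens "Given, we were going to recruit novices for both groups". It adds possible drop-out, a rule of thumb on observations per variable in regression models, and recording problems, and ends: "we decided to measure 25 participants per group". No effect size, power or drop-out rate is given for 25.

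Randomisation is "with a 1:1 allocation ratio". Under Intervention Description, both groups have the same total number of trials and the same training time (90 trials in each of 15 sessions). The sections on discontinuing interventions and on missing data exclude anyone who misses a training session or a test.

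Background and Rationale expects sensorimotor rhythm to be higher in the variable group. For EEG coherence under equal practice it says "we may expect that pairing electrodes in specific regions will be undifferentiated". Statistical Methods plans between-group comparisons of coherence, sets no equivalence margin, and leaves Bayesian versions of the tests optional.

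**The concern.** A power figure is meaningful only for the contrast whose effect went into it. Here the effect is a difference between experts and novices, while the label on the calculation is constant against variable practice. Two groups of novices who train for the same time on overlapping tasks need not differ by anything like that amount, and the document gives no reason to expect it.

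The section sees the mismatch and responds with a larger number, but it does not say what that number can detect. The only power statement in the protocol therefore belongs to a comparison that the trial will not make. A reader has no basis for judging how informative a null result would be. That matters most for coherence, where the background section itself expects the groups to look alike.

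**Working it through.** **Inputs from the protocol.** Power 0.80; 95% confidence, read as alpha 0.05; ratio 1:1; minimum 4 per group; chosen size 25 per group. **Assumed, because not stated:** two-sided testing, a two-sample comparison, and the numbers of completers and pre-post correlations used below.

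**1. The plan's own figure.** The source means and SDs are not printed, so 4 per group cannot be reproduced forward. It can be inverted. With n = 2(1.960 + 0.842)²/d² per group, d = 2.802 × √(2/n).
- n = 4: d = 2.802 × √0.5 = 1.98.
- n = 3: d = 2.802 × √0.667 = 2.29.

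A rounded-up answer of 4 therefore implies d between 1.98 and 2.29. Other methods give:

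| Method | d implied by 4 per group |
|---|---|
| Normal, two-sided | 1.98 to 2.29 |
| Normal, one-sided | 1.76 to 2.03 |
| t-test, two-sided | 2.38 to 3.07 |

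The implied difference is roughly 2 SD or more in nearly every variant.

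**2. What the chosen size detects.** The normal formula at n = 25 gives d = 2.802 × √(2/25) = 0.79. The noncentral t gives 0.81. With fewer completers (noncentral t):

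| Per group analysed | d for 80% power |
|---|---|
| 25 | 0.81 |
| 20 (assumed) | 0.91 |
| 17 (assumed) | 0.99 |

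**3. Power at 25 per group over a range of effects.** The document gives no novice-versus-novice effect, so this is a range: 18% at d = 0.3, 41% at 0.5, 79% at 0.8 and 93% at 1.0 (two-sample t-test at one time point).

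**4. Effect of using the pre-test.** With pre-post correlation r and equal SDs, the SD of change is √(2(1 − r)) times the single-time SD. The baseline-adjusted residual SD is √(1 − r²) times it.

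| r (assumed) | d for 80%, change | d for 80%, baseline-adjusted |
|---|---|---|
| 0.5 | 0.81 × 1.000 = 0.81 | 0.81 × 0.866 = 0.70 |
| 0.7 | 0.81 × 0.775 = 0.63 | 0.81 × 0.714 = 0.58 |

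At d = 0.5 and r = 0.7, power is 61% on change and 68% with baseline adjustment. At r = 0.5 the change analysis gives 41%, as at a single time point. A change analysis gains only if r exceeds 0.5; baseline adjustment gains if r exceeds 0.

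**5. The coherence expectation.** With an observed difference of zero at 25 per group, the 95% interval is ±2.011 × √(2/25) = ±0.57 SD. For two one-sided tests at 0.05 with a true difference of zero, the margin giving 80% power is about (1.645 + 1.282) × √(2/25) = 0.83 SD by the normal formula. Simulation with an estimated SD gives 79% at ±0.83, 81% at ±0.85 and about 10% at ±0.5.

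**The case against.** The strongest reply is that the protocol makes no false claim about 25 per group. It attaches 0.8 only to the minimum, says openly that both groups are novices, and multiplies the number more than sixfold, partly for that reason. That stands: the defect is an unquantified increase from an unsuitable base, not a claim of 80% power at 25.

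A reader might go further in three ways that the document does not support.

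- **That 4 per group is an arithmetic error, since a t-test at d = 1.98 to 2.29 falls short of 80%.** That reasoning is circular. It derives d from a normal formula and then tests it with another method. The source values are not shown, and if the true input is d = 2.38 or more, 4 per group is right.
- **That moderate differences would usually be missed.** The 41% at d = 0.5 is for a single time point. Repeated-measures ANOVA is planned for the MRI outcomes, and at a pre-post correlation of 0.7 power at d = 0.5 is 61% to 68%. The statement depends on a correlation that the protocol does not give.
- **That 25 per group cannot support a finding of similar coherence.** This depends on a margin, and none is set; about ±0.85 SD is feasible. The expectation is a hedged background remark about coherence only, next to a predicted difference in sensorimotor rhythm. Nowhere does the protocol say that non-significance will be read as equality.

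The regression rule of thumb is one example among several reasons, and the list of tests for motor proficiency is open-ended. Little should be made of it.

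**Conclusion.** The concern holds in limited form. The power of 0.8 belongs to an expert-versus-novice difference of roughly 2 SD or more. The trial compares two novice groups, for which 25 per group gives 80% power at about 0.81 SD, or about 0.91 SD with 20 completers. These figures assume two-sided 0.05 and a two-sample t-test, and 20 is an illustration. Exclusion for any missed session or test makes some loss plausible, but no rate is given. The detectable difference falls with a change analysis only if the pre-post correlation exceeds 0.5, and with baseline adjustment if it exceeds 0. Whether the 4-per-group figure was computed correctly cannot be judged from the document. The coherence point is secondary: a non-significant test would not by itself show similarity, but the protocol does not say it will be used that way.

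**What to change.** In the Sample Size section, remove the 4-per-group figure as the basis for power and state what the chosen size delivers. Suggested text: *With 25 participants per group, a two-sided two-sample t-test at the 5% level has 80% power for a standardised between-group difference of about 0.81; if 20 per group complete (assumed), about 0.91.* If a change or baseline-adjusted analysis is intended, give the smaller detectable difference with the assumed pre-post correlation beside it. It would also help to name the outcome to which the statement applies.

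If similar coherence is to be concluded, say that it will rest on a confidence interval against a stated margin, or on a Bayes factor with a stated criterion. Note that 25 per group gives about 80% equivalence power only for a margin near ±0.85 SD, and about 10% at ±0.5 SD.

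The cost is wording only. No further participants are needed; the downside is a less favourable stated figure.
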